##### Secondary analyses

These consist of the quantification of the incidence of postoperative delirium and measured changes in the assessed laboratory parameters including NSE, S-100β and cortisol, and the lowest Nu-DESC scoring (of at least 1 point) after surgery. The delirium assessment tools will be evaluated for their reliability. It will be compared if the results of the various assessment tools correlate with diagnosis of delirium.

##### Interim analyses

No interim analyses are planned for this study.

##### Deviation(s) from the original statistical analysis plan

Statistical analyses will begin after all study participants have been recruited for the study. If for whatever reason substantial deviations of the analysis, as outlined in this section, are needed, the responsible Ethics Committees will be informed immediately. All deviations from the analysis detailed in the protocol will be listed and rationalised in the final statistical report.

#### Handling of missing data and drop-outs

Data from study participants who have received the study drug as part of one of the four treatment arms and who were assessed for delirium as declared and who have not been treated in the ICU following surgery can be integrated in the analysis of the primary endpoint. All missing data will be documented in the CRF and described in detail within the publication. Missing values on the secondary endpoint will not be assigned (complete case analyses).

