### Interventions

Participating patients are randomly allocated to one of four study groups: one receiving haloperidol, one receiving ketamine, one receiving both haloperidol and ketamine, and one receiving placebo (Table 1). Patients are administered the active comparator or the placebo comparator only once right before the induction of anaesthesia. Three follow-up days are scheduled beginning on the first postoperative day.

**Table 1 Tab1:** Overview of treatment arms

Treatment arms	Assigned interventions
Active comparator: haloperidol	Haloperidol 0.005 mg/kg body weight at induction of anaesthesia
Active comparator: ketamine	Ketamine 1 mg/kg body weight at induction of anaesthesia
Active comparators: haloperidol + ketamine in combination	Haloperidol 0.005 mg/kg body weight + ketamine 1 mg/kg body weight at induction of anaesthesia
Placebo comparator	Normal saline (NaCl 0.9%)

The study period consists of enrolment, allocation, post-allocation and closeout (Table 2). Allocation is defined as the time point at which the patient is randomised to one of the four treatment arms. Closeout is defined by either the last day of in-hospital follow up or the follow up assessed by a telephone call in the case of preterm hospital discharge.

**Table 2 Tab2:** Weight-dependent dosing

Haloperidol: 5 μg/kg body weight diluted in NaCl 0.9%, haloperidol 5 mg/ml concentrate					
Weight (kg)	Haloperidol (mg)	NaCl (ml)	Weight (kg)	Haloperidol (mg)	NaCl (ml)
40–50	0.5	19.5	71–80	0.8	19.2
51–60	0.6	19.4	81–90	0.9	19.1
61–70	0.7	19.3	91–100	1.0	19.0
Ketamine: 1 mg/kg body weight diluted in NaCl 0.9%, ketamine 50 mg/ml concentrate					
Weight (kg)	Ketamine (mg)	NaCl (ml)	Weight (kg)	Ketamine (mg)	NaCl (ml)
40–50	50	19.0	71–80	80	18.4
51–60	60	18.8	81–90	90	18.2
61–70	70	18.6	91–100	100	18.0

The investigators will preoperatively and postoperatively test cognitive function with the Mini Mental Status Examination (MMSE), the Delirium Observation Scale (DOS), the Nursing Delirium Screening Scale (Nu-DESC) or the Intensive Care Delirium Screening Checklist (ICDSC) (Fig. 1). In addition, preoperative and postoperative cortisol, neuron specific enolase (NSE) and S-100 calcium-binding protein B (S-100B or S-100β) levels will be measured. If the study participant is discharged from the hospital before the scheduled 3 follow-up days are terminated he or she will be contacted by telephone and the conversation will be documented in a free-text field on the case report form.

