### Outcomes

#### Primary outcome measure

Superiority of one of the active comparator treatment arms in patients after surgery for prevention of hypoactive, hyperactive or mixed delirium, which is assessed by 2-point drop in MMSE score when assessed during one of the 3 postoperative days.

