### Data collection

All participants in the study will be provided a participant information sheet describing the study and providing sufficient information to enable the participant to make an informed decision about their participation in the study. The patient information sheet and the consent form will be submitted to the competent ethics committee to be reviewed and approved. The formal consent of a participant, using the approved consent form, must be obtained before the participant is subjected to any study procedure. The participant should read and consider the statement before signing and dating the informed consent form and should be given a copy of the signed document. The consent form must also be signed and dated by the investigator (or his designee). The signed form will be retained as part of the study records.

The patient will be informed on the possibility to withdraw their data from the study at any time and without needing to provide any explanation. In the case of discontinuation from trial participation, the data collected (i.e., measured laboratory values) will be used for publication if the patient does not object. In the case of deviation from the study protocol, patient data will be destroyed and thus not used for publication. Patients discharged from the hospital before the 3-day follow up post-surgery will be contacted by phone to assess their wellbeing. The collected data will be used for publication in these cases.

Data will be entered into a web-based electronic case report form (eCRF) established by the CTC Zurich (secuTrial®). Paper case report forms will be used in parallel also because of possible technical difficulties. Trial staff will have exclusive access 24 h per day, 7 days per week, to the electronic case report for data entry. A unique patient identification code will be assigned electronically to every randomised patient.

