If the patient has to be treated in the ICU after surgery, the ICDSC score is documented during every shift. The ICDSC is among the most well-studied and widely implemented adult ICU delirium screening tools worldwide and has been recommended by recently updated clinical practice guidelines. The ICUs of the University Hospital of Basel routinely use the ICDSC for assessment of delirium. Based on high-quality evidence, it has been recommended for the screening of delirium in ICU by the Society of Critical Care Medicine [7]. A score ≥ 4 indicates a positive ICDSC and the presence of delirium [7, 21].

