#### Planned analyses and sample size rationale

##### Primary analysis

Differences among the four groups will be analysed by the chi-square test. Post hoc the groups will be compared by pairwise chi-square test including the Bonferroni correction.

We will follow the intention-to-treat principle. Data on all study participants who have received the study drug as part of one of the four treatment arms will be analysed.

When the sample size in each of the four groups is 50, the 0.05-level chi-square test will have 80% power to detect a difference in proportions characterised by variance (V) of proportions:

V = Σ(π_i_- π_0_)^2^/G of 0.0125 and an average proportion of 0.35

Since study participants will be excluded from the primary analysis if there is a significant decline in MMSE score of at least 2 points during at least 1 of the 3 postoperative days or if they are treated in the ICU after surgery. The determined sample size following power analysis will be increased (see above). This might lead to an uneven number of study participants distributed over the four treatment arms after termination of the study, an occurrence that will need to be taken into consideration.

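### The primary analysis claims intention-to-treat but removes ICU-treated participants after randomisation and dosing, which can bias the comparison and lowers power

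*Protocol article*

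**What the plan says.** Three statements in the protocol article define who enters the primary comparison.

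- Primary analysis, opening: "We will follow the intention-to-treat principle", followed by "Data on all study participants who have received the study drug as part of one of the four treatment arms will be analysed".
- Primary analysis, closing paragraph: participants leave the primary analysis on either of two grounds, the second being "or if they are treated in the ICU after surgery".
- Handling of missing data and drop-outs: dosed participants enter the primary endpoint only if they are among those "who were assessed for delirium as declared and who have not been treated in the ICU following surgery can be integrated".

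The primary outcome is delirium, "which is assessed by 2-point drop in MMSE score when assessed during one of the 3 postoperative days". ICU patients are not left unmeasured. Under Delirium assessment tools: "If the patient has to be treated in the ICU after surgery, the ICDSC score is documented during every shift", and a score of 4 or more is taken to show delirium. For early discharge, the Interventions section says "he or she will be contacted by telephone and the conversation will be documented in a free-text field on the case report form", and Data collection adds "Patients discharged from the hospital before the 3-day follow up post-surgery will be contacted by phone to assess their wellbeing".

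On size, the Sample size section asks for 188 participants for 80% power, raised to 200 for drop-outs. The Primary analysis section attaches 80% power to 50 per group, that is, to all 200.

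**The concern.** The study drug is given once, just before induction. Whether a patient then goes to the ICU, and whether the assessments are completed, is settled afterwards and may depend on the drug. The Background section lists agitation as a side effect of both drugs, and confusion, hallucinations, tachycardia and hypertension for ketamine. A set chosen on such later events is no longer the set that was randomised. A drug that changed ICU use could have that effect hidden, or could appear to prevent delirium because its delirious patients were taken out of the count.

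The protocol expects such patients. Cardiac, thoracic and vascular surgery are eligible, and the Primary analysis section foresees uneven arms after exclusions without saying how they will be handled. The second filter, assessment in the declared manner, is not defined: it could mean at least one postoperative MMSE or a full three-day series. As written, two different primary sets can both be defended from the text once the data are known.

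**Working it through.** **1. The texts side by side.** An analysis of all dosed participants and an analysis of dosed, non-ICU, assessed participants cannot both be the primary analysis. The first is stated once, the ICU exclusion twice. This needs no assumption.

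**2. Reproducing the plan's power.** Inputs from Primary analysis: four groups, 3 df, alpha 0.05, V = 0.0125, average proportion 0.35. The noncentrality is λ = N × V / [p(1 − p)] = N × 0.0125 / (0.35 × 0.65) = N × 0.0125 / 0.2275. At N = 200, λ = 10.99 and power is 80.3%, so the stated 80% reproduces. The smallest N reaching 80% is 199.

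**3. Power after exclusions.** The exclusion rates are assumed, since the document gives none. Exclusions are taken as balanced across arms, with V and the average proportion unchanged.

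| Excluded from 200 | Analysed | Power |
|---|---|---|
| 0% | 200 | 80.3% |
| 5% | 190 | 78.1% |
| 6% | 188 | 77.6% |
| 10% | 180 | 75.6% |
| 20% | 160 | 70.0% |

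The 6% row is the plan's own allowance: (200 − 188)/200 = 6%. On the Primary analysis inputs, 188 does not deliver 80%, so the step from 188 to 200 provides no working reserve. The 188 may rest on a different calculation. The placebo rate behind the 30% reduction is not stated, so this cannot be checked.

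**4. Possible bias.** Assume no drug effect, true delirium 35% in both arms, and a fraction q of delirious patients removed. The observed rate is (0.35 − 0.35q)/(1 − 0.35q).

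- q = 0.1: 0.315/0.965 = 32.6%
- q = 0.2: 0.280/0.930 = 30.1%
- q = 0.4: 0.210/0.860 = 24.4%

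Equal q gives a difference of 0. For 10% v 20% it is 2.5 points, and for 10% v 40% it is 8.2 points.

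A second illustration removes whole ICU groups rather than delirious patients only. The observed rate is (0.35 − s × r)/(1 − s), with ICU share s and ICU delirium risk r. With r = 60% and s = 5% v 15%: 0.32/0.95 = 33.7% and 0.26/0.85 = 30.6%, a difference of 3.1 points. With r = 50% or 70% it is 1.9 or 4.3 points. With equal shares and equal risk it is 0.

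**The case against.** Much can fairly be said on the other side.

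- **Bias is not certain.** A reader might infer that the exclusion does bias the result, by around 8 points. The documents do not support that. Bias requires ICU treatment, or risk among those removed, to differ by arm. The 8-point figure assumes that only delirious patients are removed, with a fourfold imbalance. This limit stands.
- **The loss need not exceed the allowance.** A reader might infer that exclusions will overrun the 12-patient reserve. No ICU rate is given, high ICU risk is an exclusion at entry, and a 5% loss would be 10 patients. The bracketed carve-out for standard procedure in that criterion is itself unclear. This stands, although the reserve does not hold 80% power on the Primary analysis inputs in any case.
- **Untestable patients.** A reader might infer that patients too delirious for the MMSE have no outcome. Delirium assessment tools deducts a point for each question not answered or task not carried out, so an attempted test yields a low score and can count as an event.
- **Early discharge.** A reader might infer that these patients are dropped. Data collection says their data will be used, and a telephone contact is an accepted closeout. No MMSE by telephone is described, so their classification on unobserved days is unclear, but exclusion is not stated.
- **ICDSC is not the primary instrument.** True: retaining ICU patients means a second scale defines the event for some of them. That is a cost of the remedy and does not justify removing patients after randomisation.

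None of this answers the direct contradiction over ICU-treated participants.

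**Conclusion.** The point holds for the ICU exclusion. The article states intention-to-treat for all dosed participants and then removes ICU-treated participants from the primary analysis on a condition that arises after randomisation and dosing, although delirium is recorded for them every shift. The filter on assessment is ambiguous rather than a proven exclusion.

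The rule can bias the comparison. The illustrations run from 0 to about 8 points, all on assumed removal rates, and the documents cannot say where in that range, if anywhere, the trial lies. The power loss follows from the plan's own V and average proportion: about 199 analysed participants are needed for 80%, and only the exclusion rate is assumed. Because the rule decides who is in the primary comparison, it should be corrected before analysis.

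**What to change.** - Define the primary set as all randomised participants who received study drug, in their allocated arm, with no exclusion for ICU treatment. This is strictly a modified intention-to-treat set and should be named as such.
- Prespecify how ICU patients are classified: MMSE where obtainable, otherwise ICDSC of 4 or more as an event.
- State that patients unable to perform the MMSE are scored under the item rule in Delirium assessment tools, and mark where that rule ends and the ICDSC rule begins.
- Classify early-discharged patients on the days observed, with a sensitivity analysis for the missing days.
- Do not count DOS of 3 or more alone as an event: the article requires an additional tool to interpret it.
- Report the non-ICU, fully assessed set as a sensitivity analysis.
- Reconcile Sample size, Primary analysis and Handling of missing data and drop-outs, and restate power for the number expected to be analysed. If exclusions were kept, 80% would need 199/(1 − d) recruited: 210 at 5%, 222 at 10%, 249 at 20%.

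When the exclusion sentence in Primary analysis is rewritten, its other ground needs attention too: it names an MMSE decline of at least 2 points, which is the primary event itself. The destruction of protocol deviators' data under Data collection is a further departure from the principle. Both are separate points.

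Cost: no new data are needed, only revised wording and the sensitivity analyses. A second scale defines the event for some ICU patients. With 171 patients already recruited by August 2017, the change must be notified to the Ethics Committees and listed in the final report, as the section on deviations from the analysis plan requires.

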### Data monitoring

No regular monitoring visits at the investigator’s site are planned by the sponsor. The eCRF will be monitored daily by a member of the study team. The source data/documents will be accessible to monitors, and questions will be answered during possible monitoring. The CTC Zurich will enable monitoring at the study centres. The monitoring follows designated standard operating procedures (SOP).

### Adverse events

Individual participants will be excluded from the study in the case of an adverse event that in the opinion of the sponsor contraindicates study drug administration (emergency setting).

### Serious adverse event (SAE)

An SAE is classified as any medical occurrence that results in death, is life-threatening, requires prolongation of existing hospitalisation, or results in persistent or significant disability/incapacity. The occurrence of SAEs will be assessed based on the bedside visit and study of vital and laboratory parameters and will be recorded daily on the eCRF.

All changes in research activity and unanticipated problems will be reported to the competent Ethics Committee by the sponsor and the principal investigator. An SAE or a serious unexpected adverse drug reaction (SUSAR) must be reported within 7 days maximum if fatal, otherwise within 15 days. An annual safety report will be provided by the sponsor.

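### The SAE definition omits new hospitalisation, so a readmission after early discharge that meets no other criterion is not an SAE, and the planned telephone call is not named as an SAE source

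*Protocol article*

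**What the plan says.** The section Serious adverse event (SAE) defines the term: "An SAE is classified as any medical occurrence that results in death, is life-threatening, requires prolongation of existing hospitalisation". The list closes with the disability criterion, so its second half reads "requires prolongation of existing hospitalisation, or results in persistent or significant disability/incapacity". That makes four criteria, and the only one about hospital care presupposes a patient who is still admitted.

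The same section states how SAEs are found: "The occurrence of SAEs will be assessed based on the bedside visit and study of vital and laboratory parameters", with daily recording on the eCRF. It sets reporting limits for an SAE or SUSAR of 7 days if fatal and 15 days otherwise. It also says that unanticipated problems go to the ethics committee.

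On follow-up, the Interventions section says: "Three follow-up days are scheduled beginning on the first postoperative day". For a participant discharged sooner, "he or she will be contacted by telephone and the conversation will be documented in a free-text field on the case report form". Data collection gives the purpose: "Patients discharged from the hospital before the 3-day follow up post-surgery will be contacted by phone to assess their wellbeing", and adds that the data collected in these cases will be used. Interventions also makes the call an end point of the study period: "Closeout is defined by either the last day of in-hospital follow up or the follow up assessed by a telephone call". Neither the timing of the call nor the number of calls is stated.

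**The concern.** The definition was written for someone who stays in hospital throughout follow-up, but the protocol foresees participants who do not. For them, whether an event counts as serious depends partly on whether they had already gone home when it happened.

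What is at stake is consistent safety reporting. Participants are aged 65 or older, and the Electrocardiogram section treats QT prolongation after haloperidol as enough of a concern to repeat the ECG 48 h after surgery. An event that sends such a patient back to hospital within days of the study drug is one a reader would expect the SAE process to capture.

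**Working it through.** The protocol states no figure on this point, so the check sets its sections side by side.

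1. **Who can be out of hospital inside the window.** Follow-up covers postoperative days 1 to 3, and Interventions and Data collection both provide for earlier discharge. A discharge on day 1 and a readmission on day 2 is therefore within the design.

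2. **Classification.** Take one event that is not fatal, not life-threatening and not disabling, but needs inpatient care.
   - Participant still in hospital, stay lengthened by the event: the prolongation criterion is met, so it is an SAE.
   - Participant already discharged, readmitted for the event: there is no existing stay to prolong and no other criterion applies, so it is not an SAE.
   - Participant readmitted for an event that is fatal, life-threatening or disabling: it is an SAE by one of the other criteria.

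   The gap is the second case only.

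3. **Reporting.** The 7- and 15-day limits attach to SAEs and SUSARs. The event in the second case is non-fatal, so the 15-day limit would have applied had it been an SAE. As the text stands, the SAE limit does not start.

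4. **Ascertainment.** The bedside visit cannot reach a participant at home, and no vital signs or laboratory values are described for one. The call can reach them, but it is described as a wellbeing call recorded as free text, and the SAE section does not mention it. Because a call can be the closeout and its timing is open, a readmission after the call but still within day 3 would fall outside every contact described, apart from the 48 h ECG. The article does not say how discharged participants attend that ECG.

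5. **Size.** The documents give neither an early-discharge rate nor a readmission rate. The expected number of affected events is:

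   N × P(discharged early) × P(readmitted within the window and no other criterion met)

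   With N = 200, and assuming 10–30% discharged early and 1–5% of those readmitted in this way:
   - low end: 200 × 0.10 × 0.01 = 0.2 events
   - high end: 200 × 0.30 × 0.05 = 3 events

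   Both ranges are assumptions for illustration. Only N comes from the protocol.

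**The case against.** Several counter-arguments have force.

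- **The call exists.** It is planned for exactly these participants, is documented on the case report form, and could well reveal a readmission. A reader might infer that nobody looks for such events, but the documents do not support that. They support only that the call is unstructured and not tied to SAE assessment.
- **Other criteria still apply.** A reader might infer that no readmission after discharge is ever an SAE. That is wrong: one that is fatal, life-threatening or disabling qualifies, and a serious arrhythmia might do so as life-threatening.
- **There is another reporting route.** The SAE section sends unanticipated problems to the ethics committee, so a readmission that became known could be reported that way. It cannot be said that such events would go unreported, only that the SAE rule and its limits do not cover them.
- **This is a journal article.** A call script and safety procedures are commonly left to the full protocol, and the Research ethics approval section commits the trial to good clinical practice. This answers any complaint about missing call questions. It does not answer the definition, which the article states as a complete list and which does not fit the trial's own follow-up.
- **The change comes late.** By August 2017, 171 of 200 participants had been recruited, leaving at most 200 − 171 = 29. A change applied only to them would classify events differently in early and late participants. This stands, and the fix has to deal with it.

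**Conclusion.** The point holds in a limited form. As written, a readmission within the 3-day window that meets none of the other three criteria is not an SAE, while a comparable event that prolonged a stay is. The SAE section does not name the one contact that reaches discharged participants, so such a readmission may be missed or remain only in a free-text field. This is a defect in a stated rule, and it follows from the wording without any numerical assumption.

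The number of events cannot be derived from the documents and is probably small. Two larger claims should not be drawn. Early discharges (20 to 60 participants if 10–30% of 200 is assumed) are not the number affected, because most would not be readmitted. Nor can a distorted comparison of SAEs between arms be claimed: the outcome and analysis sections describe no such comparison. The matter deserves correction because it concerns safety reporting and is cheap to put right, not because it threatens the primary result.

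**What to change.** Three steps in the protocol article and the trial procedures:

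1. In the SAE section, widen the hospital criterion so that an event counts if it requires inpatient hospitalisation or prolongs an existing one.
2. In the same section, name the planned telephone contact as an SAE source and add a question on readmission to the call, so that Interventions, Data collection and the SAE section agree.
3. Review the free-text call records of participants already enrolled and classify any readmission under the widened definition, so that one rule applies from the first participant to the last.

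If the full protocol already contains the wider criterion, the first step is only a correction to the article. The cost is one phrase, one question on a call already planned, a short record review and perhaps a few more SAE reports. Treatment, endpoints and sample size are unchanged. The review in step 3 can recover only what the calls happened to record, and the safety report should say so.
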